#### 3.2 Investigational Product (treatment, device) and Indication

Standard treatment arm: Prednisone, a synthetic glucocorticoid with intermediate duration of action (biological half-life 18-35 hrs). The detailed characteristics of the compound, marketed under several brand names, can be found at [www.swissmedicinfo.ch](http://www.swissmedicinfo.ch): Prednison Streuli (Swissmedic registration number: 29349); Prednison Axapharm (Swissmedic registration number: 58761); Prednison Galepharm (Swissmedic registration number: 50821). In Germany, the compound is also marketed under several brand names, e.g. Prednison Galen (registration number for 5 mg strength: 33644.00.00), Prednison Decortin (registration number for 5 mg strength: 8452.00.00), or Prednison Acis (registration number for 5 mg strength: 49572.00.00).

Interventional treatment arm: matching placebo.

#### 3.3 Preclinical Evidence

Not applicable.

#### 3.4 Clinical Evidence to Date

The clinical research data pertaining to the current protocol is discussed under chapter 3.1.

---

### 3.5 Dose Rationale / Medical Device: Rationale for the intended purpose in study (pre-market MD)

At the time of inclusion, patients must be on a dose low enough to permit an abrupt stop, but high enough to still suppress the HPA axis. Based on these considerations, the planning committee settled on a daily dose of  $\geq 7.5$  mg prednisone-equivalent at the time of inclusion and on a total treatment duration of  $\geq 28$  days, with a minimal cumulative dose of 420 mg, as prerequisite for eligibility.

### 3.6 Explanation for choice of comparator (or placebo)

Although ideally chosen for the standard arm in a noninferiority trial, there is no published standard, “best-of-care” glucocorticoid tapering scheme, but a large variety of expert opinions. Accordingly, for many inflammatory and autoimmune disorders, there are no specific guidelines as to the tapering regimens. Also, there are no controlled data indicating the superiority, with respect to clinical outcome of the underlying disease, of one particular tapering scheme over another, or of tapering versus abrupt stopping. These facts and our own observations in COPD patients with biochemically suppressed adrenal glands have led us to hypothesize that, in patients chronically treated with glucocorticoids, the clinical outcome will not be worse if glucocorticoids are stopped abruptly than if they are tapered over as long as 4 weeks. This hypothesis can only be tested in a randomized, placebo-controlled trial. Hence we chose placebo as comparator. This is ethically justifiable because the dangers of clinically relevant secondary adrenal failure are small (see chapter 3.1. above). Should signs and/or symptoms of glucocorticoid deficiency nevertheless occur, or should the patient encounter circumstances with increased needs for glucocorticoids (e.g. an acute illness) or undergo a stressful procedure (e.g. an operation), glucocorticoid cover is given as per protocol.

### 3.7 Risks / Benefits

Potential risks:

In the standard treatment (prednisone) arm, the potential risks are those of unwarranted and prolonged glucocorticoid therapy, in particular: weight gain, osteopenia/osteoporosis, hyperglycemia, hypertension, muscle catabolism, increased susceptibility to infections due to immunosuppression, and suppression of the endogenous cortisol production by the adrenals.

In the intervention (placebo) arm, there is a potential risk of flare-up of the inflammatory disorder (although this is not based by high-grade evidence), and of unforeseen glucocorticoid requirements, be it due to flare-up of the underlying disease, glucocorticoid deficiency, or glucocorticoid withdrawal syndrome. The risk of endangering the patients is offset by the ease of glucocorticoid stress prophylaxis and cover in case of signs and symptoms of hypocortisolism, for which patients will be instructed and provided with an emergency dose of five 10 mg tablets of prednisone.

Trial participants in both treatment arms may be at risk for severe courses of coronavirus disease-19 (COVID-19), be it due to immunosuppression following longstanding glucocorticoid treatment prior to study enrolment, or due to iatrogenic hypocortisolism, or both. While COVID-19 vaccination is not mandatory for trial participation, patients should be encouraged to undergo vaccination. All participants are carefully instructed regarding emergency glucocorticoid therapy. This so-called stress prophylaxis should also be taken by the patient should post-vaccination symptoms of viral disease occur, but not routinely in order not to jeopardize efficacy of the vaccine. The “TOASST” trial will be conducted in accordance with all current instructions by the competent authorities.

Potential benefits:

The main overall benefit of this trial is the generation of high-level evidence about the feasibility and safety of rapid glucocorticoid withdrawal in comparison with a tapering regime, as no published data on this topic exists from randomized controlled trials.

In the intervention (placebo) arm, there is the potential benefit of reducing the cumulative prednisone dose, thereby minimizing the exposure to as well as untoward effects of glucocorticoids. Other benefits include the generation of evidence regarding the potential of the 250 mcg ACTH test to stratify patients regarding the need for tapering and the prediction of future glucocorticoid demand; as well as regarding the correlation of biochemical and clinical parameters of adrenal insufficiency.

We know of no competing trial to our study.

### 3.8 Justification of choice of study population

Patients will be recruited outside emergency situations, and no vulnerable participants will be recruited.

The eligible study population consists adult ( $\geq 18$  year-old) patients who are under glucocorticoid treatment due to an autoimmune or inflammatory disease for which tapering schemes are not standardized, such as rheumatoid arthritis, polymyalgia rheumatica, giant cell arteritis, brain edema due to tumor metastases, sarcoidosis, asthma, autoimmune hemolytic anemia, inflammatory bowel disease, and other disorders. The treating physician will decide whether the activity of the underlying disorder permits a potential abrupt treatment stop. At the time of inclusion, patients must be on an oral dose low enough to warrant the abrupt stop, but high enough to still suppress the HPA axis, i.e. corresponding to  $\geq$  mg prednisone-equivalent daily. Glucocorticoid therapy must have lasted for at least 28 days prior to inclusion and amounted to a cumulative dose of  $\geq 420$  mg prednisone-equivalent. The average daily dose must be  $\geq 7.5$  mg prednisone-equivalent.

---

Patients are not eligible to participate in the trial if they are treated with glucocorticoids for primary adrenal failure or to prevent solid or transplant graft rejection, if they are pregnant, if they are incapable or unwilling to administer glucocorticoid cover treatment in situations of stress, or if the systemic depot glucocorticoids were administered by an non-oral route (e.g. intramuscular, epidural).

## **4. STUDY OBJECTIVES**

### **4.1 Overall Objective**

To perform the first adequately powered randomized, placebo-controlled, multicenter noninferiority trial, comparing rapid termination of systemic glucocorticoid treatment with a tapering regime over 4 weeks.

### **4.2 Primary Objective**

The primary objective of this trial is to establish the feasibility and safety of rapidly terminating systemic glucocorticoid treatment, irrespective of biochemical status of the HPA axis.

### **4.3 Secondary Objectives**

The secondary objectives of this trial are:

- To establish the clinical relevance of the 250 mcg ACTH (Synacthen®) stimulation test.
- To establish the relationship between clinical signs and symptoms of hypocortisolism and biochemical adrenocortical performance

### **4.4 Safety Objectives**

The study aims to assess the safety of rapidly terminating chronic glucocorticoid therapy in a setting where patients are instructed about the signs and symptoms of hypocortisolism and provided with an emergency dose of five 10 mg tablets of prednisone to cover increased glucocorticoid needs.

---

## 5. STUDY OUTCOMES

### 5.1 Primary Outcome

The composite primary outcome is:

Time to first occurrence of hospitalization, death, initiation of unplanned systemic glucocorticoid therapy, or adrenal crisis (defined as glucocorticoid-responsive hypotension or shock with or without accompanying symptoms and signs such as weakness, apathy, nausea, vomiting, abdominal pain, hypothermia, hyponatremia [serum sodium < 135 mM], hyperkalemia [serum potassium > 5 mM], hypoglycemia [plasma glucose < 3.5 mM]); whichever occurs first.

### 5.2 Secondary Outcomes

1. Time to first occurrence of individual components of the primary outcome;
2. Cumulative overall systemic glucocorticoid dose;
3. Cumulative systemic glucocorticoid dose administered to treat or prevent adrenal failure;
4. Cumulative systemic glucocorticoid dose administered to treat relapse of disease, specified for each disease;
5. General health status as self-assessed by the participant on a visual analog scale (VAS) from 0 to 100, assessed at days 1, 7, 28, 35, 90, 180;
6. Score of symptoms and signs of hypocortisolism: weakness, hypothermia, nausea, vomiting, abdominal pain, fatigue, dizziness (assessed in structured interviews at time points: days 1, 7, 28, 35, 90, 180). Blood pressure (supine and standing) is assessed day 1 in all participants, but due to limited resources only in a subgroup of 180 patients living near their respective study center on days 7 and 35.
7. Performance in 250 mcg ACTH (Synacthen®) test: test assessed day 1 in all participants, plus days 7 and 35 in a subgroup of 180 patients,
8. In patients hospitalized at study entry: length of hospital stay.

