| Study design:                   | Randomized controlled noninferiority trial.                                                                                                                                                                                                                                                                                                                                                                                                                                                                                                                                                                                                                                                                                                                                                                                                                                                                                                                                                                                         |
| Inclusion / Exclusion criteria: | 
Patients with a variety of inflammatory disorders will be eligible, e.g. sarcoidosis, inflammatory bowel disease, polymyalgia rheumatica, rheumatoid arthritis, giant cell arthritis, autoimmune hemolytic anemia, and other autoimmune disease.
 
Inclusion criteria: Age <math>\geq</math> 18 years; daily glucocorticoid dose <math>\geq</math> 7.5 mg prednisone-equivalent at the time of inclusion; therapy over <math>\geq</math> 28 days with a cumulative glucocorticoid dose <math>\geq</math> 420 mg prednisone-equivalent prior to inclusion; tapering not or no longer mandatory to treat underlying disease.
 
Exclusion criteria: Primary adrenal failure; pregnancy; treatment with systemic depot glucocorticoids (e.g. intramuscular, epidural); incapability to administer glucocorticoid cover treatment in situations of stress; inability or unwillingness to provide informed consent; untreated hereditary galactose intolerance or lactase deficiency or glucose-galactose malabsorption.
 |

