## 6. STUDY DESIGN

### 6.1 General study design and justification of design

This is an investigator-initiated, placebo-controlled, multicenter noninferiority trial, comparing rapid termination of systemic glucocorticoid treatment with a tapering regime over 4 weeks.

**Rationale.** To date, there are no published RCTs comparing glucocorticoid tapering with rapid stopping, with regard to hazards resulting from adrenal failure or to disease relapse. Data from trials comparing different tapering schemes in patients treated for inflammatory or autoimmune disorders are scarce and inconclusive. A systematic review found “insufficient evidence about the efficacy and safety of different glucocorticoid withdrawal regimens” and demonstrated “a research gap of high quality randomized trials in a wide range of chronic disorders.” The review evaluated 9 trials (Crohn’s disease: 1; graft versus host disease: 1; bronchial asthma: 5; COPD: 2), 7 of which included less than 50 patients. Our own literature search in PubMed has produced no systematic reviews or meta-analyses published after the report by Richter et al. Given the very small scientific evidence base for the common clinical situation of glucocorticoid withdrawal and the potential for serious untoward effects of these drugs, a noninferiority trial should be conducted to test the hypothesis that an inferior outcome will not result from abrupt glucocorticoid stop even in the presence of biochemically suppressed adrenal glands. From our previous own data, we have no evidence that abrupt withdrawal will endanger patients even in the presence of biochemical adrenal insufficiency. However, it is important to note that potential hazards of adrenal insufficiency will not be underestimated in our trial. Treating physicians will be informed about their patients’ participation in the trial, and patients will be instructed on when and how to use rescue glucocorticoids. These safety measures were also taken in the “REDUCE” trial (cf. paragraph 5.4. above).

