### 9.2.2 Assessment of secondary outcomes

The secondary outcomes will be assessed using telephone interviews with patients. Questionnaires will be used to assess outcomes, as described above (see 9.2.) Treating physicians will be contacted by telephone to inquire about the secondary outcomes, cumulative systemic overall glucocorticoid dose, cumulative systemic glucocorticoid dose to treat or prevent adrenal failure, cumulative systemic glucocorticoid dose to treat relapse of underlying disease; as well as the primary outcome component of death, where applicable.

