#### 11.4.3 Secondary Analyses

Secondary outcomes:

**Performance of the 250 mcg corticotropin stimulation test.** If this test is clinically relevant, it is assumed that in patients with a normal test result, the two study arms will not differ with regard to the primary outcome, whereas patients with a pathological test result will experience an event more often after the rapid termination (experimental arm) than after tapering (control arm). It is thus hypothesized that there is an interaction between the test result and the glucocorticoid withdrawal scheme. To test for a significant interaction, the Cox proportional hazard regression model used to assess the primary objective is extended by the stimulation test result (passed vs. failed) and its interaction with the treatment group (rapid vs. tapering). If a significant interaction is found, subgroup analyses are performed for the two treatment groups in order to estimate the strength of the association between test result and primary outcome.

---

**The time to first occurrence of individual components** of the primary outcome is, in analogy to the (composite) primary outcome, also analysed with Cox proportional hazards regression models.

Cumulative overall systemic glucocorticoid dose, cumulative systemic glucocorticoid dose administered to treat or prevent adrenal failure, cumulative systemic glucocorticoid dose administered to treat relapse of disease (specified for each disease), general health status as self-assessed by the patients on a VAS, blood pressure (supine and standing), hospital length of stay, weakness, hypothermia, nausea, vomiting, abdominal pain, and fatigue are analysed with linear regression models.

In all analyses, the variables for which randomisation was stratified (center and age group) are included as covariates for adjustment. If model assumptions are not met, transformations of outcome variables and the use of generalised linear (instead of linear) models are considered.

Besides the secondary outcomes, potential glucocorticoid-induced side effects will be assessed and documented on the CRF. Proportions of side effects will be compared between treatment groups and analyzed using logistic regression.

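### Secondary outcome 4 (relapse-directed glucocorticoid dose) is defined disease by disease, and no comparison of the arms over all patients is named

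*Protocol*

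**What the plan says.** Section 5.2, item 4, defines the outcome as "Cumulative systemic glucocorticoid dose administered to treat relapse of disease, specified for each disease". The synopsis repeats this under its main secondary outcomes. The other two dose outcomes (overall dose, and dose for adrenal failure) carry no disease qualifier.

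Section 11.4.3 keeps the qualifier in the analysis text: "cumulative systemic glucocorticoid dose administered to treat relapse of disease (specified for each disease" stands in a list of variables that closes with "abdominal pain, and fatigue are analysed with linear regression models". On adjustment, the same section says that "the variables for which randomisation was stratified (center and age group) are included as covariates for adjustment". Underlying disorder is not among the covariates. It appears only as one of the pre-specified subgroup factors.

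The set of diseases is not fixed. Section 3.8 gives as examples "rheumatoid arthritis, polymyalgia rheumatica, giant cell arteritis, brain edema due to tumor metastases, sarcoidosis, asthma, autoimmune hemolytic anemia, inflammatory bowel disease, and other disorders", which is eight named conditions and a residual group. The synopsis gives "sarcoidosis, inflammatory bowel disease, polymyalgia rheumatica, rheumatoid arthritis, giant cell arthritis, autoimmune hemolytic anemia, and other autoimmune disease", which is six and a residual group.

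Section 9.2.2, on data collection, drops the qualifier: the treating physician is asked for the "cumulative systemic glucocorticoid dose to treat relapse of underlying disease".

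**The concern.** Relapse is one of the two hazards on which the trial is motivated. Section 6.1 bases the need for the study on the lack of randomised comparisons "with regard to hazards resulting from adrenal failure or to disease relapse", and section 11.2 builds the 40% event rate on expected relapse rates. Outcome 4 is the only listed outcome that isolates treatment for relapse.

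If it is analysed only within diseases, each estimate rests on a small part of the trial. In a noninferiority setting, a row of wide intervals that all include zero is easily misread as showing no excess relapse treatment after an abrupt stop. If p-values were attached to each disease, one of them could instead fall below 5% by chance. A single comparison over all patients avoids both problems, and the protocol does not say that it will be made.

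If a pooled regression was intended, the stated covariates suit it poorly. Relapse dose can be expected to differ between disorders, and differences that are not modelled add to the residual variance.

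**Working it through.** **Inputs.** From section 11.2: 573 patients, 1:1 allocation, 40% event rate, 13-point margin, 10% drop-out, 80% power, 5% significance level. Disease groups: seven (synopsis list) or nine (section 3.8 list). Equal group sizes are an assumption. The protocol gives no disease mix and no standard deviation for dose, so precision is expressed in units of a common within-disease SD.

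**1. The plan's own figure.** The critical hazard ratio is log(0.60 − 0.13)/log(0.60) = 1.478, as stated. The Schoenfeld formula at that ratio gives 206 events; 206/0.40 = 515; 515/0.90 = 572.2, which rounds up to 573. The sample size is reproduced. It concerns the primary outcome; no figure is given for outcome 4.

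**2. Precision.** With n patients per arm:
- half-width of the 95% confidence interval = 1.96 × √(2/n) SD
- difference detectable with 80% power = (1.96 + 0.842) × √(2/n) SD

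| Analysis | n per arm | Half-width (SD) | Detectable difference (SD) |
|---|---|---|---|
| All patients | 573/2 = 286.5 | 0.16 | 0.23 |
| Seven equal groups | 573/14 = 40.9 | 0.43 | 0.62 |
| Nine equal groups | 573/18 = 31.8 | 0.49 | 0.70 |
| A disease with 10 per arm | 10 | 0.88 | – |

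With k equal groups the interval widens by √k: 2.6-fold for seven and threefold for nine. For a true difference of 0.5 SD, power is about 52% with 32 per arm and over 99% with 286 per arm. With 516 completers (573 × 0.90) the half-widths are 0.17 SD pooled, 0.46 SD for seven groups and 0.52 SD for nine.

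The pooled row assumes that disease differences are removed from the residual, which is why disorder has to be in the model. That costs six to eight degrees of freedom out of more than 500.

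**3. Chance findings, if each disease were tested at 5%.** For independent tests, 1 − 0.95^7 = 0.30 and 1 − 0.95^9 = 0.37.

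**4. Whether another outcome isolates relapse.**
- Unplanned glucocorticoid therapy (a primary component, also analysed alone) merges disease flare with cortisol deficiency: section 8.3 lists both as indications.
- Outcome 3 covers adrenal failure only.
- Outcome 2 mixes all reasons. If it counts study drug, which the protocol does not settle, the taper arm receives 7 × 7.5 + 7 × 5 + 7 × 2.5 + 4 × 2.5 = 115 mg by design (sections 8.1.3 and 8.2.2) and the placebo arm none. An average excess of relapse treatment of up to 115 mg per patient after an abrupt stop would then not show as a higher overall dose.

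**The case against.** The strongest reply is that the qualifier may only mean a breakdown reported beside the total. Section 11.4.3 mentions no separate models, no test per disease and no alpha per disease. Section 9.2.2 collects a single relapse total per patient. Section 11.4 leaves detailed methodology to an analysis plan that is not shown, and section 11.4.3 allows transformations and generalised linear models. The time to unplanned glucocorticoid therapy is analysed over all patients and is driven partly by relapse. In so mixed a population, a breakdown by disease is also a sensible thing to report.

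Much of this stands. A reader might infer that the plan commits to about nine separate tests, that it leaves no overall estimate of relapse treatment, or that the trial could not show an overall increase. The documents support none of these. The disease lists are open and differ between sections, and section 6.1 further excludes disorders, with giant cell arteritis as its example, where tapering below 7.5 mg is recommended. No test by disease is stated, and the recorded data allow a pooled estimate.

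The reply does not remove the gap. The qualifier is part of the outcome's definition in the synopsis and in 5.2, so this is not only an analysis detail, and 11.4.3 attaches it to a modelled variable. No sentence names a pooled comparison. If the choice to pool were first made late, it could look data-driven.

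**Conclusion.** The point holds as a gap in definition that is cheap to close. The protocol defines relapse-directed dose by disease, names no comparison of the arms over all patients, and omits underlying disorder from the covariates. Read literally, it yields only disease-level estimates with intervals about 2.6 to 3 times as wide as a pooled comparison would give (0.43 to 0.49 SD against 0.16 SD), and wider still in the smaller diseases.

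These figures rest on seven to nine equal groups, a common within-disease SD and a normal approximation. Relapse doses will probably be skewed with many zeros, so the approximation is rough in small groups. The false-positive chance of 30 to 37% applies only if every disease is tested at 5%, which is not planned in the text. The primary analysis and the sample size are not affected.

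**What to change.** In the synopsis, section 5.2 item 4 and section 11.4.3:

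- Define outcome 4 as the cumulative systemic glucocorticoid dose given for relapse of the underlying disease, over all patients.
- Compare the arms in one model with underlying disorder as a factor, in addition to the stratification variables.
- Report disease-specific means by arm with confidence intervals, labelled as descriptive.

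This is a change of wording. The relapse dose is already recorded per patient, and underlying disorder is already needed for the pre-specified subgroups. The one downside is that disease-specific results become descriptive, which fits the precision they can have.
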